#### Potential risks or burdens for research participants and how to minimise them

No risks or burdens are expected from the basic periodontal examination and treatment. Minor pain or discomfort may follow the subgingival debridement and can be easily controlled by using a 0.2% chlorhexidine digluconate solution rinse and, if needed, paracetamol 2 × 500 mg up to four times a day for the first 2 days. The surgical interventions are also standard routine procedures and will be carefully planned and performed under local anaesthesia. The following post-operative regime will be followed in the first and second weeks following the completion of the treatment in order to minimise the patient’s discomfort and risk of complications: post-operative pain will be controlled with paracetamol if required, and all patients will be instructed to discontinue locally tooth brushing at the surgical site to minimise trauma and to rinse with 0.2% chlorhexidine digluconate two times/day for the first 2 weeks.

Adverse events (AEs) which may be related to periodontal surgery, GTI images and other dental or non-dental (including sample collection) procedures may be recorded on the AE log based on the study medical team assessments. AEs which are assessed by the study medical team as deviating, i.e. in severity, intensity and frequency, from potentially expected AEs will be recorded on the AE log. Potentially expected AEs are commonly reported AEs following non-surgical and surgical periodontal therapy such as gingival bleeding, bruising and swelling in the first 2–3 days post-therapy and increase in tooth sensitivity in the first 1–2 weeks post-therapy.

Any serious adverse event (SAE) occurring to a research participant will be reported to the sponsor within 24 h of learning of the event and to the Research Ethics Committee (REC) within 15 days if the Chief Investigator (CI) considers the event to be related to the study research procedures and unexpected.

Risk considerations for this study include the following:*Safety of patients’ sensitive data*: We will mitigate this by following the current information governance regulations. All patients’ data held will be coded and anonymised, encrypted and physically stored in a protected (locked or in a cloud) data location.*Safety of dental and other procedures*: All dental or other procedures (including radiographs and sample collection) proposed in this study fall within the scope of mainstream periodontal treatment. Furthermore, all clinical treatment will be performed by an appropriately trained clinician. In case of any unfavourable AE or adverse reaction, the study medical team will assess its severity, relatedness and potential consequences to the study patients and will make an informed decision as per the affected patient’s suitability to remain in or be exited from the study. Should the patient be exited from the study, he/she will be offered appropriate periodontal or dental treatment and any other support as needed.*Risk of not being able to complete the study due to lack of patient recruitment*: Careful analysis of patient flow and current experience from other studies has estimated that 66 suitable patients could be screened and enrolled in 6–7 months. If not, the study recruitment period will be extended, or other contingencies will be sought after including opening more sites if needed.

Reporting of any suspected expected or unexpected SAEs will be communicated to the study sponsor following standard research governance protocols as well as to the REC approving this study. The study monitoring will be performed by the clinical research facility manager and/or the study coordinator in pre-determined intervals as per the monitoring and management plan. Annual and safety reports to the REC will be submitted annually, and the REC will be notified of any corrective actions or mitigations and contingencies planned or implemented as necessary.

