The sample size calculation was based on the assumption that the proposed modified MINST protocol is an acceptable alternative to the M-MIST protocol (non-inferiority), with the advantage of reduced costs and morbidity. A non-inferiority margin of 1 mm is considered to be the largest difference that is acceptable between MINST and M-MIST (a lower threshold than the expected difference in bone gain between regenerative surgeries and open flap debridement in intrabony defects) [12] for MINST to be adopted in clinical practices because of the associated advantages of MINST. Single-flap approaches such as M-MIST have previously been reported to lead to radiographic bone gains from 1.8 ± 1.2 mm [37] to 2 mm [38] to 3.5 ± 1.0 mm [14] in small trials. MINST has been reported to lead to 2.4 ± 2.1 mm radiographic bone gain in a retrospective study [17]. Therefore, we assume that the two protocols lead to the same bone gain for the sample size calculation. Accounting for a 10% drop-out rate and using a pooled standard deviation of 1.27, recruiting *n* = 66 participants will be sufficient to confer 90% power to reject the inferiority null hypothesis. Should the true mean bone gain difference between MINST and M-MIST be 0.19 mm in favour of M-MINST, the study would retain a statistical power of 80%. The primary outcome analysis will compare the intrabony defect depth between treatment groups at 15 months using a general linear analysis of covariance (ANCOVA) model with treatment as a factor and the corresponding baseline value as a covariate and adjusting for pre-specified prognostic baseline factors (age, FMPS, BMI, defect angle, tooth mobility). For the primary efficacy endpoint, non-inferiority of M-MIST to MINST could be claimed if the lower limit of the 95% confidence interval (for the difference in mean change of radiographic intrabony defect depth change) is greater than − 1.0 mm. The primary outcome analysis will be the per-protocol analysis; the intention-to-treat analysis will be considered as the sensitivity analysis. For other non-inferiority endpoints the per-protocol analysis will also be considered the main analysis. The superiority endpoint will be analysed on an intention-to-treat basis. Subject-based and site-based analyses will be conducted. The PROM analysis will be based on linear or logistic regression (for continuous/categorical variables) comparing PROM scores or categories of scores at follow-up (3, 9 and 15 months post-intervention) between the two groups, accounting for the respective scores at baseline. We will also look at the minimally important difference for PROMs where applicable, such as in the case of the OIDP, and whether any difference between the two groups is clinically meaningful.

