#### Blinding

Due to the nature of the intervention, only blinding of all outcome examiners is possible. Both participants and clinicians administering treatment will be unblinded. Members of the Trial Steering Committee and other study team members will remain blinded to treatment allocation until the randomisation code is broken (after the last follow-up data are recorded and the database locked).

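### Ordinary adverse events are logged only at discretion and early morbidity measures are not matched between arms, so the morbidity advantage that partly supports the 1 mm margin cannot be compared without bias

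*Protocol article*

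**What the plan says.** The section on potential risks or burdens sets two levels of recording for non-serious events. Events that could be related to surgery, imaging or other procedures "may be recorded on the AE log based on the study medical team assessments". The duty comes in the next sentence: "AEs which are assessed by the study medical team as deviating, i.e. in severity, intensity and frequency, from potentially expected AEs will be recorded". The expected events are then named as those commonly reported after either kind of therapy: "gingival bleeding, bruising and swelling in the first 2–3 days post-therapy and increase in tooth sensitivity in the first 1–2 weeks post-therapy".

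Serious events follow a separate and mandatory route: "Any serious adverse event (SAE) occurring to a research participant will be reported to the sponsor within 24 h".

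The statistical analysis plan section presents MINST as an acceptable alternative "with the advantage of reduced costs and morbidity". It describes 1 mm as the largest acceptable difference "for MINST to be adopted in clinical practices because of the associated advantages of MINST", and also places the margin against an efficacy benchmark: "a lower threshold than the expected difference in bone gain between regenerative surgeries and open flap debridement in intrabony defects".

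On blinding: "Both participants and clinicians administering treatment will be unblinded". The same section says that other study team members stay blinded. It does not say which group the study medical team belongs to.

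**The concern.** A non-inferiority claim for a less invasive treatment asks the reader to weigh a possible loss of efficacy, here up to 1 mm of bone gain, against something gained. Lower morbidity is one of the gains named. Short-term bleeding, bruising, swelling and sensitivity are where such a gain would most plausibly appear, and these are the events that the rule leaves optional.

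This is a rule that the article states, not a detail left to a fuller document. Two things follow from it. The log may miss ordinary events. A difference between arms in what is logged may also reflect who was seen, when, and how the discretion was used, and not what patients experienced.

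**Working it through.** The plan gives no incidence of adverse events, so there is no figure to reproduce. The check sets the sections side by side.

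**1. The recording rule.** The first sentence permits logging; the second requires it for deviating events only. An event of an expected type, within its stated time window and of ordinary severity, falls under the first sentence alone. This covers all four named types, in both arms. No threshold defines deviating. One of its criteria is frequency; if that means frequency across patients, it cannot be judged when ordinary events need not be logged.

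**2. What else captures early morbidity** (Table 1 and the sections on clinical assessment, patient-reported outcomes, medical history and the imaging substudy).

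| Measure | MINST arm | Control arm |
|---|---|---|
| Patient-reported outcomes, days 1 and 5 | imaging subgroup only | imaging subgroup only, after initial non-surgical treatment |
| Patient-reported outcomes, 1 week after surgery | no counterpart | yes |
| Patient-reported outcomes, 3, 9, 15 months | yes | yes |
| Early healing index after treatment | none | 1 week after surgery |
| Sensitivity scale | visits 1, 4, 6, 8; visits 2a and 2b in the imaging subgroup | same; none at visits 4a to 4c |
| Concomitant medication | throughout | throughout |

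The day 1 and day 5 measures follow the initial treatment in both arms, so they compare MINST with conventional scaling, not with surgery. In operated controls the first sensitivity score after surgery is at the 9-month visit. If surgery follows soon after the 3-month visit (an assumption), that is about 9 − 3 = 6 months later, whereas the article expects sensitivity in weeks 1 to 2.

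**3. Size of the imaging subgroup.** With 2:2:1:1 allocation its share of each arm is 1/(2 + 1) = one third, or 33/3 = 11 of 33. The text says 10. So 33 − 11 = 22, or 33 − 10 = 23, patients per arm have no measure at days 1 and 5.

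**4. Contact.** Table 1 has 8 visits common to all, 2 for the imaging subgroup and 3 for operated controls: 8 + 2 + 3 = 13, which reproduces the stated range of 8 to 13. Scheduled visits are therefore:
- MINST without imaging: 8
- MINST with imaging: 8 + 2 = 10
- operated control without imaging: 8 + 3 = 11
- operated control with imaging: 13

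A MINST patient outside the imaging subgroup has no scheduled review between the side II treatment and 3 months. An operated control is reviewed at 1 week and at 1 month after surgery.

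**5. Effect of discretion.** Let p be the true share of patients with an ordinary event, and λ the chance that it is logged. The logged share is p × λ, and the ratio between arms is (p₁/p₂) × (λ₁/λ₂). It shows the true ratio only if λ₁ = λ₂, and nothing in the rule makes them equal.

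As an illustration only, with values that are not in the documents, take p = 40% after surgery and 15% without. With λ anywhere from 0 to 1 in each arm, the logged shares run from 0 to 40% and from 0 to 15%. The logged difference then runs from 0 − 15 = −15 to 40 − 0 = +40 percentage points, around a true difference of 40 − 15 = 25.

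**The case against.** The strongest reply is that the adverse event log is not the only record of morbidity. Patient-reported outcomes are a named secondary outcome, sensitivity has its own 0 to 10 scale, analgesic use is recorded, and serious events must be reported to the sponsor whether or not they are expected. Full protocol version 1.2 and the case report forms are not shown and may solicit symptoms. All of this stands, and it rules out several stronger readings that a reader might infer:

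- That morbidity is not captured at all. It is captured in part.
- That the log would show next to nothing. Permission to log is not a ban, and no section says that the discretion will go unused. Expected events are also bounded by time and severity; outside those bounds logging is required.
- That unblinded clinicians decide what is logged. The article does not equate the study medical team with the treating clinicians. An event reviewed after surgery or at suture removal would often reveal the arm, but that is an inference.
- That the margin rests on morbidity alone. Cost and an efficacy benchmark are also cited.

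The reply does not close the gap. The other early measures are control-only or subgroup-only, the all-patient ones come too late for events lasting days or weeks, and medication records do not show bleeding, bruising or swelling. A log kept by one rule is the natural common instrument, and it is the one left to discretion.

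**Conclusion.** The point holds in limited form. Ordinary short-term adverse events need not be logged in either arm, and the early measures that could stand in for the log are not matched between arms. The morbidity advantage that partly supports the 1 mm margin therefore cannot be compared without bias from discretionary logging and unequal contact.

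The extent is four named event types in both arms, no measure at days 1 and 5 in about two thirds of each arm, and 8 against 11 scheduled visits outside the imaging subgroup. The number of unlogged events and the direction of any bias cannot be determined from the documents. The primary radiographic analysis is unaffected; what is weakened is the benefit side of the argument for accepting non-inferiority.

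The conclusion assumes that the article's rule is the one applied and that unseen case report forms do not already solicit these events at matched times.

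**What to change.** Make recording mandatory for all adverse events, expected or not, under one rule in both arms, and keep the deviating judgement only as a flag for expectedness.

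Use the same short checklist (bleeding, bruising, swelling, sensitivity and pain, with severity and duration) over a fixed window after each active treatment: side I, side II and, where done, surgery. The window should cover the 2 weeks that the article itself names for sensitivity. A take-home form returned at the next scheduled visit would serve. A checklist filled in only at existing visits would not, because it would give operated controls early review and leave most MINST patients to long recall. Tabulate the results by arm, per treatment episode and per patient, so that the added burden of surgery is visible.

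The change concerns data capture and leaves care as it is. It costs a form, slightly more data entry and one table in a 66-patient trial. Participants know their treatment, so self-report carries some bias of its own; a common form and window at least make the conditions of reporting the same in both arms.

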### Study design/plan

All patients will be recruited from the Restorative and Periodontal new patient clinics at Barts and The London Dental Hospital, where potentially suitable new periodontitis patients will be informed about the study. Then a member of the research team will approach potentially interested patients, will provide more information about the study procedures together with the benefits and risks of participation and will give suitable patients the patient information sheet, which they will be advised to read carefully. Potential participants will be informed that they will be allowed to withdraw their participation at any stage of the study. The patients will then be contacted within 1 week to enquire about their willingness to take part in the study and to give them the opportunity to ask any questions about it. Upon agreeing to partake, they will be offered a baseline appointment. Written informed consent (including clinical procedures and collection of study samples) will be obtained before enrolment. Informed consent will follow the Barts and The London Dental Hospital and Queen Mary University of London (QMUL) standard operating procedures and will be conducted by staff trained in taking consent.

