#### Radiographic analyses

Standardised radiographs of selected study sites will be taken at baseline and at the 9 and 15 months follow-up visits using the parallel technique with a customised holder and an occlusal platform, which will allow a cold-cure acrylic resin occlusal registration to be made (bite index), facilitating relocation of the holder and preserving the projection geometry in subsequent radiographs. Aluminium step wedges will be used as a densitometric reference in an attempt to minimise errors due to variation in exposure time and/or film processing which may result in false positive analysis [26]. The linear radiographic measurement analysis will be carried out by a single calibrated examiner using semi-automated radiographic software with specific landmarks, as described by Nibali et al. [27]. In brief, horizontal and vertical bone loss of the intrabony defects will be measured after identifying the following landmarks in periapical radiographs: CEJ on the tooth with the intrabony defect, most coronal part of the alveolar bone and most apical part of the alveolar bone crest, where the periodontal ligament space was judged to retain its normal width. The radiographs will be analysed by the same trained and calibrated examiner in a masked, random order with the use of a computer software measurement tool (Emago®, Oral Diagnostic Systems, Amsterdam, the Netherlands).

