#### Control procedure (M-MIST)

This will be performed as described in the literature [14, 28]:Scaling and root planing using conventional ultrasonic tips and curettes under local anaesthesiaPeriodontal re-evaluation and charting 3 months laterIn case of residual PPD > 5 mm, surgical access with the following protocol:Ideally, the experimental sites will be accessed with the M-MIST technique (elevation of buccal flap only with simplified or modified papilla preservation incisions, no papilla elevation) and carefully debrided.When a defect wraps around the lingual aspect of a tooth and M-MIST is not applicable, elevation of the interdental soft tissues becomes necessary and MIST becomes the preferred approach. This consists of elevation of small buccal and lingual flaps (with modified papilla preservation incision in case of interproximal space width of at least 2 mm or otherwise simplified papilla preservation [29].When the position of the residual buccal/lingual bony wall(s) is very deep and difficult or impossible to reach with the above-described minimal incision of the defect-associated interdental space, the flap(s) will be further extended mesially or distally involving one extra interdental space to obtain a larger flap reflection [29].

Should the FMPS not reach the threshold below 25% before surgery, additional oral hygiene (OH) instructions will be given before proceeding with the surgical intervention. If after three additional OH sessions, the FMPS is still not below 25%, the patient will be exited from the study as not considered suitable for surgery [30]. Measurements will be taken during surgery to characterise the defect anatomy (number of walls, depth and width). No regenerative material/devices will be applied. Flaps will be sutured with modified internal mattress sutures (and single interrupted sutures if necessary).

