#### Need for further treatment during and following study completion

Treatment to sites other than the selected ‘intrabony site’ throughout the study will consist of subgingival debridement (as allocated by randomisation in test and control patients) and supportive therapy as per protocol. The need for other surgical interventions will be reviewed following the 15 months follow-up. Should deterioration be detected during the study in any sites, where urgent need for surgery or antibiotics is needed, this will be carried out in additional visits during the study and will be documented in the Case Report Forms (CRFs). Following the 15 months follow-up, the possible need for further treatment will be assessed based on residual PPDs > 5 mm [4, 31].

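### The adverse-event rule exits patients from the study instead of stopping procedures, so a few 15-month radiographs may be lost for treatment-related reasons (minor, cheap to fix)

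*Protocol article*

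**What the plan says.** The rule is in the protocol article, section on potential risks or burdens for research participants. After any unfavourable AE or adverse reaction, the study medical team "will assess its severity, relatedness and potential consequences to the study patients" and then decides on the patient's "suitability to remain in or be exited from the study". What follows an exit is described only as care: "Should the patient be exited from the study, he/she will be offered appropriate periodontal or dental treatment", with other support as needed. No study assessment is mentioned.

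Four other places bear on the reading:

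- Control procedure (M-MIST): a control patient whose plaque score stays too high after three extra hygiene sessions is removed, in the words "the patient will be exited from the study as not considered suitable for surgery".
- Need for further treatment during and following study completion: if a site deteriorates and urgently needs surgery or antibiotics, "this will be carried out in additional visits during the study and will be documented in the Case Report Forms".
- Radiographic analyses: the standardised radiographs "will be taken at baseline and at the 9 and 15 months follow-up visits".
- Study design/plan: patients are told that "they will be allowed to withdraw their participation at any stage of the study", so the patient's own right to stop is covered separately.

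On the analysis sets, the Statistical analysis plan section says: "The primary outcome analysis will be the per-protocol analysis; the intention-to-treat analysis will be considered as the sensitivity analysis".

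**The concern.** The AE rule names two outcomes, staying in or leaving. It does not separate stopping study procedures from stopping follow-up. An exit is decided by the study team after randomisation, and relatedness to treatment is among the things weighed. The arms differ in procedures, since only controls have surgery, and treating clinicians are unblinded. The article does not say whether the team making this decision is blinded. The 15-month outcome could therefore be missing for reasons that depend on treatment.

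Two analyses could be touched. The intention-to-treat analysis is the named check on the per-protocol result, and it is meant to keep exactly such patients. The per-protocol analysis also loses a patient who had finished the allocated treatment before the event and would otherwise have qualified. An analysis plan can choose a missing-data method, but it cannot supply a radiograph that was never taken. The remedy therefore belongs in trial conduct.

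**Working it through.** **Step 1: what exit means.** The article does not define it, so I compared its uses.

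| Section | Situation | Outcome |
|---|---|---|
| Control procedure (M-MIST) | plaque score not below 25% | exited, as unsuitable for surgery |
| Need for further treatment | urgent surgery or antibiotics | extra visits within the study, recorded in the CRFs |
| Potential risks or burdens | unfavourable AE | remain in, or exited and offered care |

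The article thus separates care given within the study from leaving it. Follow-up radiographs are tied to the 9- and 15-month visits. A patient who has left has no such visit. This is the plain reading, but it is an inference.

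**Step 2: the plan's own power figure.** Inputs from the Statistical analysis plan section: N = 66, drop-out 10%, SD 1.27 mm, margin 1 mm, true difference 0, stated power 90% (80% at a 0.19 mm disadvantage). Patients per arm: 33 × 0.9 = 29.7, taken as 30. Standard error: 1.27 × √(2/30) = 0.328 mm. By normal approximation:

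- One-sided 0.05: power 92.0% at a true difference of 0, and 79.5% at 0.19 mm. This is close to the stated 90% and 80%.
- One-sided 0.025, as a two-sided 95% interval implies: 86.2% and 69.5%.

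The mismatch in alpha is a separate matter. Below I use the two-sided 95% interval and the noncentral t distribution with 58 degrees of freedom, which gives 85.1% power at a true difference of 0.

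**Step 3: illustration of size.** The article gives no AE-exit rate and no link between AEs and bone gain. I assume k = 1 or 2 net exits in one arm, counted inside the 10% allowance so that 30 per arm are observed, and a shortfall d of 0 to 1.0 mm in the bone gain those patients would have shown. The comparison is unadjusted. The arm that should have been observed has 30 + k patients, so

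shift = d × k/(30 + k).

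For example, k = 2 and d = 1.0 gives 2/32 = 0.0625 mm. The difference is taken as MINST minus M-MIST gain. Exits in MINST shift it upwards, towards a false claim; exits in M-MIST shift it downwards, costing power.

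| k | d (mm) | Shift (mm) | False non-inferiority at true −1 mm, exits in MINST | Power at true 0, exits in M-MIST |
|---|---|---|---|---|
| 1 | 0 | 0 | 2.5% | 85.1% |
| 1 | 0.5 | 0.016 | 2.8% | 83.9% |
| 1 | 1.0 | 0.032 | 3.1% | 82.7% |
| 2 | 0 | 0 | 2.5% | 85.1% |
| 2 | 0.5 | 0.031 | 3.1% | 82.8% |
| 2 | 1.0 | 0.063 | 3.8% | 80.3% |

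If the same patients were followed, the false-claim rate would be 2.5% and power 85.6% (k = 1) or 86.2% (k = 2). If exits are balanced with equal shortfalls, the shift is zero. The table is framed for the intention-to-treat comparison. It carries over to the per-protocol comparison only for exited patients who had completed their allocated treatment, and only if about 30 per arm are analysed there too.

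**The case against.** The strongest objection is that this is a single sentence in the risk section of a condensed article. How patients are followed after discontinuation is commonly left to the full protocol, which is not shown. If the point were only that a follow-up rule is absent, that would dispose of it. But the article states a rule, remain or be exited, and it is that rule which could be better. The full protocol may qualify it; the wording shown does not.

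Much of the rest stands and limits the point:

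- Exit is at the team's discretion, and staying in could include a patient who has no further procedures.
- Site deterioration, the event closest to the outcome, is already treated inside the study.
- Little treatment remains to be stopped. MINST is given at the initial treatment visits and control surgery follows the 3-month visit. The clearest case is a control patient with an AE before surgery.
- Expected AEs are bleeding, bruising and swelling for 2–3 days and sensitivity for 1–2 weeks.
- The 10% drop-out allowance may already cover a few exits.
- The plaque-score exit is mandatory and confined to controls. It is used here only to interpret the word, and its force should not be credited to the AE rule.

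A reader might infer more: that an AE forces exit, that related AEs in particular lead to exit, or that the article says data collection ends on exit. It says none of these. Relatedness is one of three things assessed, and the end of radiographs is inferred.

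**Conclusion.** The point holds as a minor one. As worded, the AE rule allows a team decision, partly informed by relatedness, to remove a randomised patient, with the probable loss of the 15-month radiograph. The intention-to-treat analysis is affected, as is the per-protocol analysis for patients who had completed treatment.

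The size is unknown and probably near zero. The illustrative maximum of about 0.06 mm, some 6% of the margin, needs two net exits in one arm, each 1.0 mm worse. Both inputs are assumptions without support in the article, and the direction of any bias is unknown. It would be wrong to conclude that the rule threatens the trial's non-inferiority conclusion or favours one arm. The case for change is that the lost data cannot be recovered and the remedy is cheap.

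**What to change.** Reword the AE sentence in the risks section along these lines: after an AE the study medical team may stop further study procedures, including planned control surgery, or give extra treatment; the patient stays in follow-up, including AE follow-up, and has the 9- and 15-month radiographs, unless he or she withdraws consent or the assessment itself is unsafe. State that these outcomes are included as observed in the intention-to-treat analysis. Membership of the per-protocol set is a separate decision: a patient who had completed the allocated treatment may qualify, while one whose surgery was cancelled may not.

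The cost is one protocol sentence and one CRF field that separates stopping procedures from stopping follow-up. The visits are already scheduled, and clinical discretion and the right to withdraw are unchanged. The downside is that a few patients treated off protocol are asked back for those visits.
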